### Intervention allocation

Participants will be randomly allocated in a 1:1 ratio* to receive the intervention, or standard patient care. *Except for immediate family member participation (see section *Randomisation*).

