
The intervention will be delivered by therapists who have received extensive training before the trial starts and will use a standardised treatment manual developed by the OPTIMISTIC team. Prior to participating in the graded activity module, the treating clinician will make a judgment as to the degree of physical activity the participant is safely capable of doing, which will be communicated to the therapists. The therapists will remain in contact with the treating clinician throughout the trial to discuss any changes. The therapists and/or the research nurse can request that the treating physician/Investigator to review the patient at any time if any of the research team, the patient or the carer have any concerns. If required, the patients’ GP will be informed.

Participants will receive a workbook containing relevant information and assignments. If deemed appropriate a patient may be given a gym membership to assist with their set goals. If participants give their permission, CBT sessions will be audio recorded and transcribed. Transcriptions will be anonymised. Audio recordings will be stored securely at local sites and destroyed as described under *Study record retention*.

Between sessions participants will do ‘home-work’ assignments that are discussed in the subsequent session. If caregivers are involved in the intervention, they will be asked to support the patient in carrying out these assignments. Treatment integrity will be determined by two experienced cognitive behavioural therapists, who will independently rate a random selection of audio-taped sessions. During the intervention period phone calls to participants will be made at least once a week between sessions to remind them to complete any homework and to ensure attendance at sessions. Where it is felt necessary and resources allow participants will be visited in their homes to increase adherence and provide support where needed.

The intervention runs for 10 months but is front-loaded, meaning the first 4 months can be considered the ‘active’ phase with the remaining 6 months in the ‘booster’ phase. In this period of 10 months a patient will receive 10 to 14 sessions; at least 5 of them are face to face sessions. For the other sessions the therapist can decide, dependent on the traveling distance and the mobility of the patient, to use telephone contact or video conferencing as an alternative.

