### Statistics and data analysis

#### Sample size calculation

The primary outcome is the DM1-Activ scale, which is a Rasch-built measure of activity and participation for patients with DM1 and is currently the best such measure for these patients. Based on a minimum clinically important mean difference of 1.4 on the 40-item DM1-Activ scale, standard deviation of 3.5 and effect size = 0.4, 80 % power and 5 % significance level, we need a sample size of 100 in each arm, or 200 in total.

DM1 is a genetic condition so it is likely that some members of the same family will take part in the study. To avoid the risk of contamination, immediate family members (mother, father, children, and siblings) will be allocated to the same group, with the first family member being randomly allocated and subsequent members being assigned to the same group as the first. This means that there will be some clusters of more than one individual and the sample size needs to be inflated to account for this. Newcastle estimates that this may affect 50 % of their participants, the other sites estimate that fewer than 10 % of participants will be part of a family group. All sites estimate that almost all family groups will comprise two individuals. Using estimates of distributions of recruitment across sites (Newcastle = 23 %; Nijmegen = 30 %; Paris = 33 %; and Munich = 13 %) and the above family group proportions gives an average cluster size of 1.17. Using a conservative intra-cluster correlation coefficient of 0.20, gives an inflation factor of 1.035, meaning the recruitment target needs to be increased by 10 to 296. After allowing for up to 30 % drop-out this gives a final sample size of 208, or 104 participants per arm.

These are conservative estimates (especially the minimum clinically important difference). The clinical OPTIMISTIC sites between them see well over 1,000 DM1 patients per year, which gives OPTIMISTIC a good pool of potentially eligible participants. Around 70 % of DM1 patients are expected to be eligible for OPTIMISTIC.

We will be using one of our secondary outcomes, the 6-minute walk test (6MWT) as an additional validation of the DM1-Activ scale, meaning that we have also powered this secondary outcome. The DM1-Activ sample size of 208 gives over 90 % power for the 6MWT based on a mean difference of 40 m, standard deviation of 80 m and a baseline of 450 m.

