#### Proposed analysis

The primary analyses will be conducted according to the principles of intention to treat (ITT) as outlined on the ICH E9 ‘Statistical Principles for Clinical Trials’.

Continuous variables will be summarised by the number of observations, number of missing values, mean, standard deviation (SD), median, inter-quartile range (IQR) and range. Summaries will be provided at baseline, at each subsequent time point and for the change from baseline by intervention group. Categorical variables will be summarised by the number of observations, number of missing values and number and percentage in each category. Summaries will be provided at baseline and at each subsequent time point.

The primary outcome and most other outcomes are continuous and so linear models will be utilised. The primary outcome of change in DM1-Activ will be analysed using mixed effects (repeated measures) regression models. Models will include fixed effects for intervention group, time point, and their interaction, plus random effects for each subject to account for repeated measures, and will assume a general covariance structure. A binary variable will be added to the regression model to represent the difference between the intervention and standard care. The minimisation variables of severity of DM1 (measured using the MIRS 5-point scale) and caregiver involvement at baseline will also be added to the regression model as fixed effects, as well as stratification by site.

Intervention effect differences will be reported with 95 % confidence intervals (CIs) and *P*-values. Results will also be explored and reported with additional *a priori* adjustment for potential effect modifiers (see list in *Measures used as potential effect modifiers*). Subgroup analyses will be carried out by first testing for a subgroup factor by intervention interaction [16]. If this is significant at the 5 % level, results will be estimated separately by the different subgroups. These analyses will also be repeated for all the secondary outcomes. Appropriate transformations of outcomes will be performed where necessary to satisfy modelling assumptions.

A statistical analysis plan (SAP) will be written prior to datalock and approved by the statistician and CI. Analyses will be carried out using SAS.

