#### Trial/study management

Each clinical site will have a research nurse or research associate allocated to the study who will oversee the study and will be accountable to the local PI. The research nurse or research associate will be responsible for checking the CRFs for completeness, plausibility and consistency. Any queries will be resolved by discussion with the CI, or delegated member of the study team. At every site a lead CB therapist will be responsible for the referral of patients to an appropriate CB therapist if they are randomised to the intervention arm. The same CB therapist will have regular meetings with the other therapists at the site and will oversee the flow of patients in the intervention arm. The CB therapist will be responsible for data collection at the clinical site with respect to the intervention.

A study-specific Delegation Log will be prepared for each site, detailing the responsibilities of each member of staff working on the study.

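### The primary model and the sample size leave out therapist clustering in the intervention arm; if outcomes vary by therapist, the primary confidence interval is too narrow

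*Protocol article*

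**What the plan says.** All references are to the protocol article.

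- **Model.** Proposed analysis describes a repeated-measures mixed model for DM1-Activ. It has fixed effects for group, time point and their interaction, adjustment for the two minimisation variables and site, "plus random effects for each subject to account for repeated measures, and will assume a general covariance structure". The only random effects named belong to the subject.
- **Delivery.** Under Behavioural change intervention: "The intervention will be delivered by therapists who have received extensive training before the trial starts". Each patient has 10 to 14 sessions over 10 months. Therapists work from a common manual and get a support call every two weeks, and a random selection of recorded sessions is rated for integrity.
- **Therapists at a site.** Trial/study management has a lead therapist at each site refer intervention-arm patients to a suitable therapist, and adds: "The same CB therapist will have regular meetings with the other therapists at the site". More than one therapist at a site is therefore expected. The number is not given.
- **Sample size.** Sample size calculation starts from a "minimum clinically important mean difference of 1.4 on the 40-item DM1-Activ scale", with "standard deviation of 3.5 and effect size = 0.4". For "80 % power and 5 % significance level, we need a sample size of 100 in each arm, or 200 in total". The only clustering allowed for is that of relatives assigned to the same arm; an ICC of 0.20 "gives an inflation factor of 1.035".

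**The concern.** Patients who share a therapist over 10 to 14 sessions may have outcomes more alike than patients of different therapists. A model with a subject effect only treats intervention patients as independent once the covariates are accounted for.

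The terms already in the plan do not cover this:

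- The general covariance structure concerns repeated measures within a subject, not different patients of one therapist.
- Site as a fixed effect takes up mean differences between sites, but not differences between therapists within a site.
- The family inflation concerns relatives in either arm, whereas therapist clustering arises in the intervention arm alone.

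Any positive therapist variance pushes the error one way, towards a primary result that looks more precise than it is. The planned sample size has almost no reserve to absorb it.

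**Working it through.** **Inputs from Sample size calculation and Intervention allocation.** Difference 1.4, SD 3.5, 80% power, 5% significance (taken as two-sided; the article does not say), family factor 1.035, and 104 analysed per arm. Allocation is equal: "Participants will be randomly allocated in a 1:1 ratio".

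**Assumed, because the documents do not give them.** Therapist ICC ρ of 0.01 to 0.05, and k = 8, 12 or 20 therapists with equal caseloads m = 104/k.

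**1. Reproduce the stated figures.**
- Per arm: 2 × (1.960 + 0.842)² × (3.5/1.4)² = 98.1, so 99. The t-test version gives 99.1, so 100, as stated.
- Family factor: 1 + (1.17 − 1) × 0.20 = 1.034 (stated 1.035).
- Recruitment: 200/0.70 = 286, and 286 × 1.035 = 296, as stated.
- Analysable: 296 × 0.70 = 207 (stated 208).

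**2. Power with no therapist variance.** Variance of the difference = 3.5² × (1.035 + 1.035)/104 = 0.2438, so SE = 0.494. Power = Φ(1.4/0.494 − 1.96) = 80.9%.

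**3. Add therapist clustering in the intervention arm only.**
- True variance = 3.5² × [1.035 + 1.035 + (m − 1)ρ]/104.
- SE ratio (true/model) = √{[2.07 + (m − 1)ρ]/2.07}. The family factor is in both SEs, so the ratio isolates the therapist effect.
- Actual type I error = 2 × [1 − Φ(1.96/ratio)].
- Power = Φ(1.4/true SE − 1.96).

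Example with k = 8 and ρ = 0.05: m = 13 and (m − 1)ρ = 0.60. The ratio is √(2.67/2.07) = 1.136. Type I error is 2 × [1 − Φ(1.726)] = 8.4%. True SE is √(12.25 × 2.67/104) = 0.561, and power is Φ(2.496 − 1.96) = 70.4%.

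| Therapists (caseload) | ICC | SE ratio | Type I error | Power |
|---|---|---|---|---|
| 8 (13.0) | 0.01 | 1.03 | 5.7% | 78.7% |
| 8 (13.0) | 0.02 | 1.06 | 6.4% | 76.5% |
| 8 (13.0) | 0.05 | 1.14 | 8.4% | 70.4% |
| 12 (8.7) | 0.01 | 1.02 | 5.4% | 79.5% |
| 12 (8.7) | 0.02 | 1.04 | 5.9% | 78.1% |
| 12 (8.7) | 0.05 | 1.09 | 7.2% | 74.0% |
| 20 (5.2) | 0.01 | 1.01 | 5.2% | 80.1% |
| 20 (5.2) | 0.02 | 1.02 | 5.5% | 79.4% |
| 20 (5.2) | 0.05 | 1.05 | 6.2% | 77.1% |

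These are normal approximations, so they ignore the degrees of freedom lost when therapists are few.

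**4. Compare with the clustering the plan does correct.** Averaged over both arms, the omitted factor is 1 + (m − 1)ρ/2. With 12 therapists and ρ = 0.01 it is 1 + 7.67 × 0.01/2 = 1.038, about the size of the family factor of 1.035.

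**5. Test what could offset the loss.**
- Baseline adjustment with an assumed correlation of 0.5 multiplies both variances by 0.75. Power is then 82.2% (k = 8, ρ = 0.05) to 88.5% (k = 12, ρ = 0.02). The SE ratio and type I error do not change.
- With no drop-out (148 per arm, k = 8, ρ = 0.05), power is 80.9%. The caseload rises to 18.5, so the SE ratio becomes √(2.945/2.07) = 1.19 and type I error 10.0%.

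**The case against.** A reader might infer that the standard error is certainly too small and that the trial will not have 80% power. The documents do not support that. They give no therapist ICC, number or caseload; only the presence of more than one therapist at a site can be read from the text. The effect runs from nil at an ICC of zero, through 80.1% power at 0.01 with 20 therapists, to a marked loss.

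The power loss is also not fixed. The 30% drop-out is an upper allowance, the article calls its inputs conservative, and baseline adjustment could more than make up the difference. This stands for power. It does not help the standard error, and with more patients per therapist the understatement grows.

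Training, the manual, integrity rating and fortnightly support calls all plausibly lower the ICC. That stands too, but they need not bring it to zero. Therapists still choose how some sessions are delivered, and the exercise programme is settled in counselling.

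Finally, the section is a proposal, and a SAP was to follow before datalock. The model description names no family effect either, although the sample size provides for families, so the list may be condensed. The SAP could therefore add a therapist term. But the article does not leave the model open: it names the fixed and random effects of the primary analysis, and as named they assume no therapist variance.

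**Conclusion.** The point holds conditionally. The stated primary model and sample size allow for no therapist variance in a design where one arm only is nested within therapists. If outcomes vary by therapist, the primary confidence interval is too narrow and the P-value too small.

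Under the assumed ICC of 0.02 to 0.05, 8 to 20 therapists and 104 analysed per arm, the true SE is 1.02 to 1.14 times the model SE. A nominal 5% test then has an error rate of about 5.5% to 8.4%, so a nominal 95% interval covers about 91.6% to 94.5%. Power is about 70% to 79%. At an ICC of 0.01 there is little loss.

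The lasting issue is the validity of the interval and P-value, since power may be recovered by other means. The size is uncertain, but the direction is known and the correction is simple, so the plan should be changed.

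**What to change.** - **Proposed analysis:** add a random therapist effect for the intervention arm only (a partially nested model with control participants as singletons). Let the residual variance differ by arm, and use Kenward-Roger or Satterthwaite degrees of freedom. Specify this before datalock, because adding the term once results are known would be open to challenge.
- **Data collection:** make sure the treating therapist's ID is recorded for each intervention participant. It may already be, as the case report form is not shown and the therapist is responsible for the intervention data.
- **Sample size calculation:** state that the 80% power assumes no therapist clustering, and show the range of power over plausible ICCs and therapist numbers.

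The cost is one model term and one ID variable. The interval will be slightly wider, the stated power less favourable, and the therapist variance imprecisely estimated if therapists are few.

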#### Missing data

The extent of missing data will be explored in the outcomes especially the primary outcome. Patterns of missing data will be explored and predictors of missingness examined, especially if these vary by intervention. If necessary, multiple imputations will be utilised to impute missing data assuming the missingness mechanism is missing at random (MAR). However, mixed models have the useful property of using all available data without resorting to imputation where data is MAR. The assumption of MAR cannot be pre-specified or tested as it depends on whether and how data has become missing. Measures should be taken where possible to minimise the extent of missing data in the recording of outcomes so that missing data is less likely.

### Transfer of data

Case Report Forms (CRF) will be developed together with the trial management team, statistician and data manager to ensure that the data management system (see *Data management system*) supports the research aims of the study. The data management system will be fully validated, including the provision of test data and supporting documentation. Data entry will be coordinated by TCTU although sites will generally be doing their own data entry. It is the PI responsibility to ensure the accuracy of all data entered and recorded in the CRF/eCRFs. Data will be stored on servers controlled by TCTU and housed at the University of Dundee. Backup-up and disaster recovery will be provided by TCTU according to its standard operating procedures.

The study questionnaires will be completed at screening/baseline, 5-month, 10-month (that is, the end of the intervention) and 6-month post-intervention onto a paper CRF with subsequent transcription (where appropriate) to OpenClinica.

All research related blood sample analysis and data established from the NHS/health care tests will be stored in an unidentifiable format in the password protected disaster recovery formatted database.

All research blood samples (link-anonymised) will be processed as per Sample Analysis and Chain of Custody Plans in the Study Operations Manual and transported to the relevant laboratories for analysis.

Patients will be informed of data storage and consent will be sought. Finally, the Delegation of Responsibilities Log will identify all trial personnel responsible for data collection, entry, handling and managing the database.

### Trial management and oversight arrangements

OPTIMISTIC will have the following two oversight committees:The Trial Management Committee will be responsible for day-to-day operational issues.The External Advisory Board will be responsible for strategic decision making and issues linked to monitoring ethical and patient safety issues, together with monitoring recruitment and data quality issues.

#### Trial management committee

The OPTIMISTIC trial will be managed by TCTU. The Trial Management Committee (TMC) will comprise the leader of the trial component of OPTIMISTIC, senior statistician, TCTU Assistant Director, a representative of TCTU’s data management staff and the TCTU senior trial manager and study trial manager. Other members of the OPTIMISTIC group may be added as required by the consortium or the Trials Unit. The TMC will meet at least monthly by face-to-face and more often if needed, especially in the early phases of the trial.

#### Trial/study management

Each clinical site will have a research nurse or research associate allocated to the study who will oversee the study and will be accountable to the local PI. The research nurse or research associate will be responsible for checking the CRFs for completeness, plausibility and consistency. Any queries will be resolved by discussion with the CI, or delegated member of the study team. At every site a lead CB therapist will be responsible for the referral of patients to an appropriate CB therapist if they are randomised to the intervention arm. The same CB therapist will have regular meetings with the other therapists at the site and will oversee the flow of patients in the intervention arm. The CB therapist will be responsible for data collection at the clinical site with respect to the intervention.

A study-specific Delegation Log will be prepared for each site, detailing the responsibilities of each member of staff working on the study.

#### External advisory board

The External Advisory Board comprises independent, international experts covering the key areas of competence required to provide oversight of OPTIMISTIC scientific activity. The list of participants is at http://optimistic-dm.eu/external-advisory-board/. The Board ensures a high standard of research and governance and monitors the progress of the project. The OPTIMISTIC consortium will consult the Board at least annually (more often if the Board requires) to get members’ opinions with regard to study progress, especially on issues linked to the trial.

The Board will comment on ethical and safety issues as well as general conduct issues. In addition the project will have access to the TREAT-NMD project ethics council (PEC) if any additional advice should need to be sought.

#### Inspection of records

The CI, PIs and all institutions involved in the trial will permit trial-related monitoring, audits, and ethical review. The CI agrees to allow each country specific sponsor or, representatives of the sponsor, direct access to all trial records and source documentation.

### Good clinical practice

#### Ethical conduct of the study

The study will be conducted in accordance with the principles of Good Clinical Practice (GCP). In addition to sponsorship approvals, a favourable ethical opinion will be obtained from the appropriate country specific ethics committee(s) and where appropriate local management approval(s) will also be obtained prior to the start of the trial.

#### Confidentiality

All laboratory specimens, evaluation forms, reports, and other records will be identified in a manner designed to maintain participant confidentiality. All records will be kept in a secure storage area with limited access by appropriate trial staff only. Clinical information will not be released without the written permission of the participant, except as necessary for monitoring and auditing by the sponsors or their designee. The CI and staff involved with the trial will not disclose or use for any purpose other than performance of the trial, any data, record, or other unpublished, confidential information disclosed to those individuals for the purpose of the trial. Prior written agreement from the sponsors or their designee will be obtained for the disclosure of any said confidential information to other parties.

#### Data protection

The CI and staff involved with the trial will comply with the requirements of the relevant data protection legislation for their jurisdiction with regard to the collection, storage, processing and disclosure of personal information. The CI and trial staff will also adhere, if appropriate, to other local regulations and policies with regard to confidentiality of data. Access to collated participant data will be restricted to the CI and appropriate trial staff.

Computers and IT systems used in connection with the trial will have access-control measures such as centrally allocated logins and passwords. Finally, published results will not contain any personal data that could allow identification of individual participants.

